### Publication process

[name] will ensure that the results of the study are published in due time after study termination. The reporting of study will follow the CONSORT extension for randomized trials of non-pharmacological trials [65].

### Changes to initial plan

In the statistical analysis plan, imputation for missing data was changed from “last observation carried forward” to “multiple imputation.” This protocol change was made before inclusion was completed, and while the study was still blinded. The BI was added as a secondary outcome before inclusion of the first patient to enable comparison with previous studies evaluating ADL during and after hospitalization [9, 10, 17, 109].

From February 2014, patients have been included from an additional municipality, the municipality of Hvidovre, due to the possibility of providing in-home training for these patients as well. Randomization in this municipality follows a 2:2 allocation. From September 2014, patients assigned to physical rehabilitation in the community have no longer been excluded from the study, as rehabilitation in the community is rarely commenced until 4 weeks after discharge and thus after the study’s primary end point. From January 2015, a physician has performed the initial screening of all eligible patients and informed the patients about the study before referring them to the primary investigator for informed consent and baseline assessments to enhance enrollment.

### Ethics

The patients will be informed that participation is voluntary and that they can withdraw at any time without losing their right to treatment. The study is approved by the Ethics Committee of the Capital Region of Denmark (H-2-2012-115) and by the Danish Data Protection Agency (2007-58-0015) and is registered at ClinicalTrials.gov (NCT01964482). The Ethics Committee will be informed about important protocol modifications for approval.

## Discussion

There is limited data on the effect of strength training initiated during hospitalization and continued after discharge in older medical patients, and details about the optimal nature and dose of exercise are needed [29, 50, 51]. Higher intensities seem superior to lower intensities in older adults [52, 110, 111], and supervision is essential for compliance [49]. This study provides a detailed description of a simple, supervised cross-continuum strength training program, based on a minimal time-consuming treatment approach. All physiotherapists involved are thoroughly instructed in the intervention to try to obtain standardization and avoid a cluster effect. The treatment approach was chosen to investigate whether as few as two well-performed strength training exercises per session, combined with protein supplementation, during hospitalization and 4 weeks after discharge, can improve mobility in older medical patients. This approach was chosen to facilitate implementation in a busy clinical care setting, given a positive trial outcome.

### Data monitoring

No data committee will be established as the intervention is considered to be low-risk. All investigators and physiotherapists will be asked to report adverse events to [name], and the study will be stopped if the adverse event is considered to be caused by training or testing. A “hotline” to an ED geriatrician has been established should an adverse event occur or should the investigators need advice regarding a patient. The authors will meet frequently during the study to discuss trial conduct.

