### Blinding

To ensure concealment of allocation, a study nurse will be in charge of the randomization procedure following the randomization list which will not be available to the investigators. If a patient is randomized to the intervention group, the study nurse will inform the involved physiotherapists about this allocation. Patients will be asked not to reveal to the investigators to which group they belong. The discharge test in the patient’s home will be conducted before the first post-discharge training session to avoid the investigator seeing the exercise equipment in the home. Moreover, 4-week follow-up assessments will take place between 4 and 5 weeks after discharge, and the study nurse will inform the investigators when patients are ready for the 4-week follow-up assessment (end of intervention) regardless of allocation, to avoid the investigators guessing who belongs to which group. Also, all training equipment will be removed from the patients’ homes before the 4-week assessment to ensure that the investigators do not see the equipment in those homes. Additionally, all contacts with physiotherapists in the hospital and in the municipalities regarding allocation, questions about the protocol and other practicalities will be undertaken by the study nurse to ensure blinding of the investigators. In the case of a possible adverse event and the unavailability of one of the co-authors to evaluate the severity of the event, the allocation of the patient can be revealed to the investigators in order to assure proper treatment of the patient. If the patient can no longer participate in assessments he/she will be excluded from the study. Otherwise, the patient will remain in the study and all information of all such events will be reported in the manuscript.

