### Study groups

#### Control group

Patients in the control group will receive routine care during hospitalization and after discharge. No efforts will be made to change this care during the study period. Routine care will be used as a comparator to reflect the current care for these patients.

According to the Danish Healthcare Quality Program (DDKM) [66], the functional level and nutritional status of hospitalized patients must be described within 24–48 h after admission [67] and treatment planned accordingly. No standard involves in-hospital training [67], but patients needing recovery (e.g. rehabilitation) should be identified [68], and rehabilitation (including exercise) should be planned to target the patient’s impairment and limitations. Often rehabilitation starts during hospitalization, and if it continues after discharge a rehabilitation plan must be prepared by the hospital. At Hvidovre Hospital around 5 % of older medical patients are discharged with a rehabilitation plan (personal communication with geriatric team in the ED, 30 October 2015) involving exercise therapy supervised by physiotherapists.

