### Intervention group

Patients in the intervention group will receive 1:1 supervised progressive strength training daily on weekdays during hospitalization and three times per week for 4 weeks (12 training sessions, 1:1 supervised) after discharge. To account for possible cancellations, i.e. due to illness or other obstacles for training completion, distributing the 12 in-home training sessions over a maximum of 5 weeks will be allowed. The training will take place in the patient’s bedroom during hospitalization and in the patient’s own home after discharge.

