### Outcome measures

Outcomes measures will be assessed on admission (baseline), shortly after discharge, approximately 4 weeks after discharge (primary end point) and 6 months after discharge. All outcomes to be assessed are presented in Table 2.

**Table 2 Tab2:** Variables to be assessed

Variable	Baseline	Discharge	4 weeks	6 months
Primary outcome				
de Morton Mobility Index (DEMMI)	+	+	+	+
Secondary outcomes				
24-h mobility (*activ*Pal3™ monitors; 1-week assessments)	+	+	+	+
Isometric knee extension strength	+	+	+	+
30-sec sit-to-stand test	+	+	+	+
Habitual gait speed (HGS)	+	+	+	+
Hand-grip strength (HG)	+	+	+	+
Activities of Daily Living (Barthel Index 20)	+	+	+	+
Descriptive variables				
Age	+			
Gender	+			
Weight	+	+	+	+
Educational level	+			
Living status	+	+	+	+
History of smoking	+			
Use of ambulatory devices	+	+	+	+
Use of municipal help	+	+	+	+
History of falls during the last year	+	+	+	+
Falls Efficacy Scale	+	+	+	+
Nutritional Risk Screening (NRS)	+	+	+	+
New Mobility Score (NMS)	+	+	+	+
Cumulated Ambulation Score (CAS)	+	+	+	+
Days per week spent outdoors	+	+	+	+
Hospitalization within last 4 weeks			+	
Hospitalization within last 6 months	+			+
Possible confounders and modifiers				
Age	+			
Gender	+			
Cognition				
Short Orientation-Memory-Concentration test (OMC)	+			
Mini Mental State Examination (MMSE)		+	+	+
Trail Making Test (Trails)		+	+	+
Digit Symbol Substitution Test (DSST)		+	+	+
Hopkins Verbal Learning Test (HVLT)		+	+	+
Geriatric Depression Scale (GDS)		+	+	+
Health status (EQ-5D)	+	+	+	+
Self-rated health (EQ-5D)	+	+	+	+
Mini Nutritional Assessment (MNA)	+	+	+	+
Self-reported physical activity	+	+	+	+
Verbal Ranking Scale (VRS)	+	+	+	+
Medications	+	+	+	+
History of training before hospitalization	+			
History of training in the municipality after discharge		+	+	+

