### Data collection

The primary investigator and a team of three assistant investigators will perform all baseline and follow-up assessments. All four investigators are trained physiotherapists with 1 to 15 years of experience.

The admission assessments will be performed on the acute medical admissions ward or on an internal medicine ward at Copenhagen University Hospital, Hvidovre, Denmark, within the first 48 h after admission. All follow-up assessments will be performed in the patient’s own home, and the same investigator will assess the same patient at all assessments whenever logistically possible, to promote patient retention.

During each training session the supervising physiotherapist will complete an exercise diary consisting of information about the level of exercise attained according to the progression models, the extra load added (kg), and the number of sets and repetitions performed at each level. Self-reported pain will be registered immediately before and after each training session by the use of the VRS. Moreover, the physiotherapist will register reasons for non-participation as well as the amount of protein consumed after each training session. The patient time line including data collection is presented in Table 3.

**Table 3 Tab3:** Patient timeline

	Study period						
Time point	Admission	Baseline	Hospital intervention	Discharge assessment	Home intervention	4-week assessment	6-month assessment
		≤48 h after admission	Daily during hospitalization	In patient’s home	3 times per week for 4 weeks in patient’s home	In patient’s home	In patient’s home
Enrollment							
Eligibility screen	X						
Informed consent	X						
Study groups							
Strength training		X	X	X	X	X	X
Control		X		X		X	X
Assessments							
Baseline assessment^a^		X					
Primary outcomes		X		X		X	X
Secondary outcomes		X		X		X	X
Descriptive variables and possible confounders and modifiers		X		X		X	X

^a^See Table 2 for a detailed description of assessed variables

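### Adverse events are reported partly by physiotherapists who attend only the training arm, so events collected this way should not be read as a between-arm comparison

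*Protocol article*

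**What the plan says.** Under Data monitoring, the article states who reports: "All investigators and physiotherapists will be asked to report adverse events to" a member of the team. The Blinding section, after describing what happens when a possible adverse event leads to unblinding, adds that "all information of all such events will be reported in the manuscript".

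The two kinds of reporter meet different patients:

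- **Investigators.** The Data collection section says: "The primary investigator and a team of three assistant investigators will perform all baseline and follow-up assessments". The Outcome measures section places the follow-up visits "shortly after discharge, approximately 4 weeks after discharge (primary end point) and 6 months after discharge". Both arms have the same visits.
- **Physiotherapists.** The Blinding section says: "If a patient is randomized to the intervention group, the study nurse will inform the involved physiotherapists about this allocation". The Intervention group section gives these patients weekday sessions in hospital and then sessions "three times per week for 4 weeks (12 training sessions, 1:1 supervised) after discharge". The Control group section says: "Patients in the control group will receive routine care during hospitalization and after discharge".

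Table 2 also schedules falls history and a pain rating at every visit in both arms, and recent hospitalization at baseline, 4 weeks and 6 months. Falls and hospitalization are listed as descriptive variables, and pain as a possible confounder or modifier. None is labelled an adverse event.

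**The concern.** The reporting rule gives one arm an extra set of observers. Suppose a control patient becomes dizzy or is injured at home two weeks after discharge. The event enters the record only if it comes up at the 4-week visit or later. The same event in a training patient can also be noticed by a physiotherapist who is in the home about three times a week and knows the allocation.

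If the reports are then published by arm, without their source, more events in the training arm could reflect closer observation, more harm, or both. Acutely ill older patients have background events whatever their allocation, so the question will arise. A later analysis cannot recover control-arm events that nobody was placed to notice.

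**Working it through.** **Inputs from the article**

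- Home sessions, training arm: 3 per week × 4 weeks = 12. This reproduces the stated 12 (Intervention group).
- Investigator visits from discharge to 4 weeks, both arms: 2, the discharge visit and the 4-week visit (Outcome measures, Data collection).
- Overlap: none. The discharge visit precedes the first home session, and the 4-week visit follows the end of training (Blinding).
- Study physiotherapist contacts in control: none planned. Around 5 % of older medical patients leave hospital with a rehabilitation plan (Control group), but community rehabilitation is said to start only rarely before 4 weeks (Changes to initial plan).
- Attendance: 80 % is the article's threshold for high compliance (Compliance). 50 % is my assumption, to show the range.

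**Formula:** ratio = (sessions attended + common visits) ÷ common visits

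| Case | Training arm | Control arm | Ratio |
|---|---|---|---|
| Full attendance | 12 + 2 = 14 | 2 | 7.0 |
| 80 % attendance | 9.6 + 2 = 11.6 | 2 | 5.8 |
| 50 % attendance (assumed) | 6 + 2 = 8 | 2 | 4.0 |
| Full attendance, discharge visit not counted | 12 + 1 = 13 | 1 | 13.0 |
| Common visits only | 2 | 2 | 1.0 |

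Weekday sessions in hospital add further contacts in the training arm only. Their number depends on length of stay, so I leave them out. Spreading the sessions ("distributing the 12 in-home training sessions over a maximum of 5 weeks will be allowed") changes their spacing, not their number.

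**What Table 2 already covers equally**

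- *Hospitalization*: the last 4 weeks at the 4-week visit and the last 6 months at the 6-month visit. This is usable for comparison.
- *Pain*: a rating at every visit. The ratings taken before and after each training session exist in one arm only and cannot be compared.
- *Falls*: asked at every visit, but labelled as the last year. At a visit 4 to 5 weeks after discharge, the time since discharge is 4/52 to 5/52 of that window, about 8 to 10 %, plus the hospital stay. Most of the window precedes randomization. Even at 6 months, about half of it does (26/52).
- *Other events*, such as dizziness or injury: no item on an equal schedule is listed.

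**The case against.** Much of the opposing case stands.

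- **No comparison is planned.** Adverse events are not among the outcomes, and the Statistical analyses section does not mention them. This is correct, so the issue is how reported events will be read, not a flawed test.
- **The Blinding sentence is narrower than it looks.** It closes a paragraph on unblinding and continued participation, and it does not promise pooled counts by arm. This stands. It is still the article's only commitment to publish adverse events, and nothing in it separates the sources.
- **The rule serves safety oversight.** Reports are gathered so that someone can judge whether training or testing caused an event, and supervisors of training are natural reporters. This stands, and physiotherapists should go on reporting.
- **An article condenses the full protocol.** How events are elicited and tabulated may be set out elsewhere, so I do not treat that as missing. The point rests on what the article does state: who reports, and which patients they see.

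A reader might go further and infer that the adverse-event reports are the trial's only safety evidence, or that fewer falls with training would go unseen. Table 2 does not support either reading, since falls, hospitalization and pain are recorded at common visits in both arms.

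A reader might also try to put a size on the false excess. With a 20 % true risk in both arms, 90 % capture with training and 50 to 70 % in control, the counts would read 0.20 × 0.90 = 18 % against 0.20 × 0.50 = 10 % to 0.20 × 0.70 = 14 %, an excess of 4 to 8 percentage points. Every one of those inputs is assumed and the article supplies none, so I draw no conclusion from them.

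**Conclusion.** The point holds in a limited form. Under the stated rule, the training arm has up to 14 scheduled reporting contacts against 2 in control between discharge and 4 weeks: 7:1 at full attendance and 5.8:1 at 80 %. In-hospital sessions widen the gap. The figures rest on two assumptions: that both the discharge and the 4-week visits count as reporting contacts, and that controls have no routine physiotherapy contact that feeds into the study's reports.

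The ratio measures opportunity to report. It does not say how many events would be missed in control, and it does not mean that counts would differ sevenfold. What follows is that events gathered through this route should not be presented or read as a comparison of the arms. The primary analysis is untouched. This is an inexpensive improvement to harms reporting, not a threat to the trial's main conclusion.

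**What to change.** Add to the Data monitoring section:

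1. Events noted by physiotherapists are reported in a separate listing for the intervention arm only, with the source named.
2. Any between-arm description of harms uses only information that the blinded assessors obtain in the same way in both arms at the planned discharge, 4-week and 6-month visits. That means the existing hospitalization item and visit pain ratings, falls asked about since the last visit, and one short standard adverse-event question.

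Physiotherapists continue to report every event for safety oversight.

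**Cost.** No visits or staff are added. There will be two listings instead of one, and some events will stay outside the comparative table. The new falls wording and the new question can apply only to visits still to come. Recruitment began in October 2013 and was expected to end in March 2016 (Study status), and the article cites a communication from 30 October 2015, so coverage will be partial and the report should say so. Separating events by source can be done for all patients, provided the reports received so far show who made them.

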### Roles and responsibilities

The study has been designed at Optimed, Clinical Research Centre, Copenhagen University Hospital, Hvidovre, Denmark. The trial is overseen by the group of authors.

### Study status

Recruitment of patients is ongoing at the time of submission of this protocol. Recruitment began in October 2013 and is expected to end in March 2016.

## Abbreviations

ADL: Activities of Daily Living
BI: Barthel Index 20
CAS: Cumulated Ambulation Score
CONSORT: Consolidated Standards of Reporting Trials
COPD: chronic obstructive pulmonary disease
DDKM: Danish Healthcare Quality Program
DEMMI: de Morton Mobility Index
DSST: Digit Symbol Substitution Test
ED: Emergency Department
GDS: Geriatric Depression Scale
HG: habitual gait speed
HGS: hand-grip strength
HVLT-R: Hopkins Verbal Learning Test – Revised
IKE: isometric knee extension strength
MCI: mild cognitive impairment
MMSE: Mini Mental State Examination
MNA: Mini Nutritional Assessment
NMS: New Mobility Score
NRS: Nutritional Risk Screening
OMC: Short Orientation-Memory-Concentration test
RM: repetitions maximum
SPIRIT: Standard Protocol Items: Recommendations for Interventional Trials
STS: 30-sec sit-to-stand test
TIDieR: Template for Intervention Description and Replication
Trails: Trail Making Test
VRS: Verbal Ranking Scale
